# Amitriptyline at low-dose and titrated for irritable bowel syndrome as second-line treatment (The ATLANTIS trial): protocol for a randomised double-blind placebo-controlled trial in primary care

**DOI:** 10.1186/s13063-022-06492-6

**Published:** 2022-07-08

**Keywords:** Irritable bowel syndrome, Amitriptyline, Primary care, Double-blind, Placebo, Randomised controlled trial

## Abstract

**Background:**

Irritable bowel syndrome (IBS) is a common functional bowel disorder that has a considerable impact on patient quality of life and substantial societal and health care resource costs. Current treatments are often ineffective. Tricyclic antidepressants have shown promise in secondary care populations but their effectiveness in a primary care setting remains unclear.

**Methods:**

ATLANTIS is a randomised, multi-centre, parallel-group, two-arm, double-blind, placebo-controlled trial of low-dose amitriptyline as a second-line treatment for IBS in primary care. Participants will be invited by letter, or recruited opportunistically, from general practices in three regions of England (West Yorkshire, Wessex, and West of England) and screened for eligibility. A total of 518 adult patients with IBS, who are symptomatic despite first-line therapies, will be randomised 1:1 to amitriptyline or identical placebo for 6 months. Treatment will commence at a dose of 10 mg (or one placebo tablet) daily at night, with dose titration up to a maximum of 30 mg at night, depending on side effects and response to treatment. Participant-reported assessments will be conducted at baseline and 3, 6, and 12 months post-randomisation. The primary objective is to determine the effectiveness of amitriptyline, compared with placebo, in improving participant-reported global symptoms of IBS at 6 months (using the IBS Severity Scoring System). Secondary outcomes include relief of IBS symptoms, effect on IBS-associated somatic symptoms (Patient Health Questionnaire-12), anxiety and depression (Hospital Anxiety and Depression Scale), ability to work and participate in other activities (Work and Social Adjustment Scale), acceptability and tolerability of treatment, self-reported health care use, health-related quality of life (EQ-5D-3L), and cost-effectiveness. A nested, qualitative study will explore patient and general practitioner experiences of treatments and trial participation, including acceptability, adherence, unanticipated effects, and implications for wider use of amitriptyline for IBS in primary care.

**Discussion:**

Determining the clinical and cost-effectiveness of low-dose amitriptyline as a second-line treatment for IBS in primary care will provide robust evidence to inform management decisions.

**Trial registration:**

ISRCTN ISRCTN48075063
. Registered on 7th June 2019.

**Supplementary Information:**

The online version contains supplementary material available at 10.1186/s13063-022-06492-6.

## Introduction

### Background and rationale

Irritable bowel syndrome (IBS) is a common, chronic disorder of gut-brain interaction. Symptoms, which include abdominal pain and altered stool form or frequency, range from mild to severe, but are often recurrent and unpredictable [1]. The prevalence of IBS in the community is between 5 and 10% [2], and the condition accounts for > 3% of all consultations in primary care [3]. Impact on quality of life and social functioning can be substantial and comparable with organic bowel disorders, such as Crohn’s disease [4, 5]. The pathophysiology of IBS is incompletely understood, there is no cure, and medical management can be challenging and unsatisfactory. Treatment is usually focused on improving symptoms and quality of life. Current first-line therapies, as recommended by the National Institute for Health and Care Excellence (NICE), include a clear explanation of the condition and information sharing on self-management, dietary and lifestyle advice, soluble fibre, laxatives, and antispasmodic or anti-diarrhoeal drugs [6]. However, if these measures are ineffective, general practitioners (GPs) are often left with few effective treatment options and patients with ongoing symptoms may be referred for a specialist opinion in secondary care [7]. New therapies for IBS continue to be developed; however, they are usually modest in terms of their efficacy and are expensive and, in recent years, several have been withdrawn due to serious concerns about side effects [8, 9].

The NICE IBS guideline states that GPs should “consider” low-dose tricyclic antidepressants (TCAs) for their analgesic effect as second-line treatment for IBS, if first-line therapies have not helped [6]. A possible mode of action is through the pain-modifying properties of low-dose TCAs [10–13] and their action on gastrointestinal motility [14, 15] rather than any effect on mood. However, survey results indicate less than 10% of GPs prescribe TCA for IBS often, and only 50% believe they are effective [16]. Although systematic reviews and meta-analyses suggest that low-dose TCAs may be effective in the treatment of IBS [17–19], important limitations exist in the current evidence. In the most recent review of 12 trials and 787 patients [18], almost all studies were conducted in specialist settings, and the duration of follow-up was limited to 12 weeks, which is insufficient for a chronic fluctuating condition. It is unclear whether these results would translate to a primary care population, and whether there would be an impact on resource use, quality of life, and social functioning. The NICE guideline highlighted the need for a randomised controlled trial (RCT) of TCAs in primary care [6]. Amitriptyline was chosen for this trial as it has shown promise in two small previous trials [20, 21]; is an established, inexpensive drug, which GPs prescribe commonly for other conditions; and has a well-characterised safety profile [22].

### Aim and objectives

The AmitripTyline at Low-dose ANd Titrated for Irritable bowel syndrome as Second-line treatment (ATLANTIS) trial aims to determine the clinical and cost-effectiveness of amitriptyline compared with placebo in patients with IBS in primary care.

#### Primary objective

To determine the effect of amitriptyline on global symptoms of IBS as measured by the IBS Severity Scoring System (IBS-SSS) [23], 6 months after randomisation.

#### Secondary objectives

To assess the effect of amitriptyline on:Global symptoms of IBS, as measured by the IBS-SSS at 3 and 12 monthsThe proportion of participants with relief of IBS symptoms, as measured by:Subjective global assessment (SGA) of relief of IBS symptoms at 3, 6, and 12 months [24]A weekly response to the question “Have you had adequate relief of your IBS symptoms?”

3.IBS-associated somatic symptoms, as measured by the Patient Health Questionnaire-12 (PHQ-12) at 6 months [25, 26]4.Anxiety and depression scores, as measured by the Hospital Anxiety and Depression Scale (HADS) at 3, 6, and 12 months [27]5.Ability to work and participate in other activities, as measured by the Work and Social Adjustment Scale (WSAS) at 3, 6, and 12 months [28–30]6.Acceptability of treatment, as measured by patient-reported choice to continue trial medication beyond 6 months7.Self-reported adherence to treatment at 3 weeks and 3, 6, 9, and 12 months8.Tolerability of treatment, as measured by self-reported adverse events (AEs) using the Antidepressant Side Effect Checklist (ASEC) at 3, 6, and 12 months [31]

#### Cost-effectiveness objectives

32To assess the effect of amitriptyline on:Self-reported health care use, as measured by a health resource use questionnaire at 3, 6, and 12 monthsHealth-related quality of life, as measured by the EQ5D-3L at 3, 6, and 12 months [32, 33]Cost-effectiveness, as measured via the incremental cost-effectiveness ratio and expressed in terms of incremental cost per quality-adjusted life year (QALY) at 6 and 12 months

#### Internal pilot objectives

To assess recruitment and 6-month follow-up rates against pre-defined progression criteria.

#### Nested qualitative study objectives

To understand patient and GP experiences of treatments and trial participation, and how these can inform our understanding of the quantitative results and future implementation in primary careTo identify factors that facilitate or impede prescribing and acceptability of, as well as adherence to, low-dose amitriptyline in this patient groupTo identify patient and GP perspectives on the broader impact of the trial, including any unanticipated effects not captured by the quantitative measuresTo explore psychosocial and contextual factors that might shape the wider use of amitriptyline for IBS

### Trial design

ATLANTIS is a randomised, multi-centre, parallel-group, two-arm, double-blind, placebo-controlled superiority trial of low-dose amitriptyline as a second-line treatment for people with IBS in primary care. Participants will be randomised 1:1 to receive amitriptyline or placebo for 6 months. At 6 months, patients will be offered the option of continuing their allocated trial medication for a further 6 months (see the “Intervention” section for protocol amendment V5.0). Participant-reported assessments are conducted at baseline, 3, 6, and 12 months post-randomisation. An internal pilot will assess pre-defined progression criteria for recruitment and follow-up rates. A nested, qualitative study will explore patient and GP experiences of treatments and trial participation.

## Methods

### Trial setting

Patients will be recruited from approximately 75 general practices, within urban and rural settings, with a range of socio-demographic and diversity characteristics, across three UK geographical regions, referred to as “hubs”: West Yorkshire, Wessex, and the West of England. Each practice is classed as a research site with a GP principal investigator (PI). Practices will be required to have obtained practice management approval and undertake a site initiation visit prior to recruiting to the trial. Patients will be directed to respond to the invitation to the main hub research team, comprising a “hub lead clinician” and research nurse or clinical study officer (CSO), responsible for coordinating patient screening and activity.

### Eligibility criteria

 Eligible patients must meet all inclusion criteria and none of the exclusion criteria listed in Table 1.

**Table 1 Tab1:** Eligibility criteria

**Inclusion criteria**
1. Aged ≥ 18 years with a diagnosis of IBS (of any subtype of stool pattern [diarrhoea, constipation, mixed bowel habit, or unclassified]) in their primary care record, and fulfilling the Rome IV criteria for IBS 2. Ongoing symptoms, defined as an IBS symptom severity score (IBS-SSS) score of ≥ 75 at screening, despite being offered dietary advice and first-line therapies, as defined by the NICE guideline (antispasmodics [e.g. mebeverine], fibre supplements [e.g. fybogel], laxatives [e.g. bisacodyl], or anti-diarrhoeals [e.g. loperamide]), assessed at screening via patient self-report 3. A normal haemoglobin, total white cell count, and platelets within the last 6 months prior to screening 4. A normal C-reactive protein within the last 6 months prior to screening 5. Exclusion of coeliac disease, via anti-tissue transglutaminase antibodies, as per NICE guidance 6. As amitriptyline is harmful in overdose, patients must have no evidence of active suicidal ideation, as determined by three clinical screening questions, and no recent history of self-harm (within 12 months prior to screening). All patients will be asked (1) whether they have experienced any thoughts of harming themselves, or ending their life in the last 7–10 days; (2) whether they currently have any thoughts of harming themselves or ending their life; and (3) whether they have any active plans or ideas about harming themselves, or taking their life, in the near future. These questions are used in preference to a formal suicidal risk rating scale, as such scales perform poorly in clinical practice. Any positive response on any of the questions will trigger an urgent GP review 7. If female, patients must be post-menopausal, or surgically sterile, or using highly effective contraception (and must agree to continue for 7 days after the last dose of the investigational medicinal product [IMP]) 8. Able to complete questionnaires and trial assessments and to provide written informed consent
**Exclusion criteria**
1. Age > 60 years with no GP review in the 12 months prior to screening (a safety criterion due to the increased risk of gastrointestinal pathology > 60 years to ensure any changes in bowel habit are IBS-related and do not require further investigation) 2. Meeting locally adapted NICE 2-week referral criteria for suspected lower gastrointestinal cancer 3. A known documented diagnosis of inflammatory bowel disease or coeliac disease 4. A previous diagnosis of colorectal cancer 5. Individuals participating currently, or who have within the 3 months prior to screening been involved in, another clinical trial of an investigational medicinal product 6. Pregnancy, breastfeeding, or planning to become pregnant within the next 18 months 7. Current use of a TCA, or use of a TCA within the last 2 weeks prior to randomisation, for another indication 8. Allergy to TCAs or any other known contraindication to the use of TCAs. The latter includes taking monoamine oxidase inhibitors, or receiving them within the last 2 weeks; already receiving a TCA for the treatment of depression; previous myocardial infarction; recorded arrhythmias, particularly heart block of any degree, or prolonged Q-T interval on an ECG; mania; severe liver disease; porphyria; congestive heart failure or coronary artery insufficiency; or receiving concomitant drugs that prolong the QT interval (e.g. amiodarone. fluconazole, or terfenadine)

### Recruitment, randomisation, and blinding

#### Recruitment

General practices interested in participating will be identified via expression of interest with the support of the local Clinical Research Networks (CRNs). Participating practices will search their patient list for potentially eligible adult patients, using a SnoMed code list developed previously (Additional file 1: example electronic health record search). Potential participants will be invited to take part via mailed letter, opportunistic recruitment during GP consultations, and advertisements for self-referral placed in participating general practices, community pharmacies, and on practice/specialist IBS organisational websites. Interested patients will either return a reply slip or contact the recruiting hub via email or telephone, or be directed to the ATLANTIS website containing a self-screening questionnaire with contact details for the local recruitment hubs. Interested patients will be screened by the hub research nurse or CSO against initial eligibility criteria on the telephone. Those identified as potentially eligible will be invited to a clinic appointment to provide informed written consent with the hub research nurse, CSO, GP research nurse, or CRN nurse (trained in good clinical practice (GCP) and trial procedures); have screening bloods taken (including a full blood count and C-reactive protein (if not tested within the previous 6 months) and anti-tissue transglutaminase antibodies for coeliac screening (if not previously tested)); and be registered into the trial (Additional file 2: Patient information sheet and consent form). In view of the potential lethality of amitriptyline in overdose, three brief screening questions will be used to identify any potential participants with suicidal ideation, who will then be referred to their GP for further assessment.

The general practice PI will review the blood test results and patient screening to confirm trial eligibility, which is further checked by the hub lead clinician. Participants confirmed as eligible will then complete the baseline questionnaires and be randomised subsequently.

#### Randomisation

Randomisation will be performed by the hub research nurse or CSO via an automated system based at the University of Leeds Clinical Trials Research Unit (CTRU). Participants will be allocated to amitriptyline or placebo via minimisation incorporating a random element to ensure the treatment arms are well balanced for depression score (HADS-depression score ≥ 8), predominant stool pattern (diarrhoea, constipation, mixed bowel habit, or unclassified), and hub. Following randomisation, an automatically generated email will be sent to the central pharmacy with instructions to dispense specific trial medication kits, depending on the participant’s allocation, which will be posted directly to the participant.

#### Masking

Neither the participant nor those responsible for their care or evaluation (the primary care team and the research nurses or CSOs) will know the treatment allocation. This will be achieved by identical packaging and labelling of both amitriptyline and placebo, and the use of unique kit codes.

The ATLANTIS trial team and CTRU personnel involved in the day-to-day running of the trial will be masked to group allocation until the final database lock. A CTRU trial safety team will have access to treatment allocation, throughout the trial duration, for participant unmasking and preparation of unmasked safety reports to the Data Monitoring and Ethics Committee (DMEC).

Participants will be able to request for themselves and their GP to be told their treatment allocation shortly after their final follow-up at 12 months, to facilitate post-trial treatment decisions. Treatment allocation will be provided via email, supported by an evidence-based leaflet developed with input from patient and public involvement (PPI) representatives, only when CTRU have confirmation that all study assessments and contacts are complete, and all required data have been received. This will remain confidential (to the participant and their GP), as far as possible, to protect and maintain the overall masking for the trial research team. Should participants need support following provision of treatment allocation, they will be directed to the ATLANTIS qualitative researcher who is independent from the day-to-day running of the trial, recruitment, data collection, and treatment decisions.

Emergency unmasking (before 12 months) may be requested on the grounds of safety, when information about the participant’s trial treatment is critical for their ongoing clinical care, by the chief investigators (CIs), local PI, authorised delegate, or treating physician. Treatment allocation will be revealed by the CTRU using code-break envelopes for office hours requests, with a duplicate copy being held at the central pharmacy for out-of-hours requests.

### Intervention

Patients will be provided with written guidance on how to titrate their trial medication. They will be advised to commence at a dose of 10 mg (one tablet) daily with dose titration over 3 weeks, up to a maximum of 30 mg at night (three tablets), depending on side effects and response to treatment. After an initial 3-week titration, it is expected that the majority of participants will remain on a steady dose, but they can modify their dose throughout the study in response to their IBS symptoms and any side effects, reflecting how amitriptyline is used in usual care. All participants consent to 6 months of trial medication. They will be offered the option of continuing their allocated treatment for a further 6 months (although this will not be offered to some later recruits due to truncated follow-up for participants who were randomised during the last 6 months of the trial).

For safety purposes, due to the risk of harmful overdose, an initial 1-month supply of trial medication will be sent to participants by the central pharmacy following randomisation. Further trial medication will be dispensed at months 1, 3, 6, and 9 (as appropriate) and ordered by the hub research nurse or CSO using the CTRU web-based kit allocation system. The hub research nurse or CSO will contact participants by telephone at weeks 1 and 3, and months 3, 6, 9, and 12 to assess adherence to trial medication and concomitant medications and provide support as needed. All participants have the option of a GP consultation approximately 1 month after commencing trial medication to provide support if they have queries or concerns.

### Relevant concomitant care permitted or prohibited during the trial

Usual care for IBS will be provided by the participant’s GP, with the exception that amitriptyline or other TCAs cannot be commenced during the trial. The use of monoamine oxidase inhibitors and drugs that prolong the QT interval (e.g. amiodarone, terfenadine, or sotalol) are prohibited for the duration of the trial.

### Provisions for post-trial care

Following trial and outcome measure completion, participants will have the option to discuss amitriptyline prescription for IBS under the care of their GP if they wish.

### Trial assessments and data collection

Required data, assessment tools, collection time points, and processes are summarised in Figs. 1 and 2. Additional file 3 provides further information on each of the outcome measures and methods of data collection. Data will be collected via paper or electronic case report forms and questionnaires or electronically via the CTRU automated registration/randomisation/kit system and the electronic software “REDCap”.

**Fig. 1 Fig1:**
[figure not shown]
Trial flow chart — participant identification and screening

**Fig. 2 Fig2:**
[figure not shown]
Trial flow chart — randomisation, treatment, and follow-up. For participants recruited following Protocol v5.0, follow-up concludes at 6 months

All participants will be asked to complete questionnaires at baseline and at 3, 6, and 12 months post-randomisation (unless recruited after protocol amendment v5.0) and to answer a weekly question “Have you had adequate relief of your IBS symptoms?” for 6 months. Participants will be sent text message and email reminders after 1 week to prompt completion. The hub trial team will telephone the patient to collect outstanding data for all outcomes for non-responders.

### Safety

Participants will self-report adverse events (AEs) to the hub research nurse/CSO via the ASEC at weeks 1 and 3 and months 3, 6, 9, and 12. All serious adverse events (SAEs) and suspected unexpected serious adverse reactions (SUSARs) will be collected throughout the study, from the time of randomisation until 7 days following discontinuation of the study drug. All reportable AEs, SAEs, and SUSARs (the latter considered highly unlikely in this trial) will be reported to the independent DMEC and relevant regulatory bodies within the required time frames, and appropriate action will be taken.

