#### Safety analyses

All participants receiving at least one dose of trial medication will be included in the safety analysis. Descriptive statistics of self-reported AEs on the ASEC will be presented by arm. The number of participants reporting a SAE and details of all SAEs will be reported for each treatment group. The number of participants withdrawing from trial treatment will be summarised by treatment arm, along with reasons for withdrawal.

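### Participants with an SAE are counted per arm over a window set by when each person stops the drug, and the tolerability objective omits the week 1 and 3 ASEC

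*Protocol article*

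**What the plan says.** All references are to the protocol article.

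**SAE window.** Under Safety, SAEs and SUSARs are "collected throughout the study, from the time of randomisation until 7 days following discontinuation of the study drug". The first part of that phrase suggests the whole study. The second, "from the time of randomisation until 7 days following discontinuation of the study drug", ends collection at a date specific to each participant.

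**SAE summary.** Under Safety analyses, "All participants receiving at least one dose of trial medication will be included in the safety analysis", and "The number of participants reporting a SAE and details of all SAEs will be reported for each treatment group". No person-time, rate or common time horizon is given. Treatment withdrawals are also summarised by arm, with reasons.

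**Length of treatment.** Everyone consents to 6 months. Under Intervention, "They will be offered the option of continuing their allocated treatment for a further 6 months", with an exception for some later recruits. The legend of Fig. 2 says that follow-up ends at 6 months for those recruited after protocol v5.0.

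**ASEC.** The secondary objectives define the outcome as "Tolerability of treatment, as measured by self-reported adverse events (AEs) using the Antidepressant Side Effect Checklist (ASEC) at 3, 6, and 12 months". Under Safety, participants report adverse events "via the ASEC at weeks 1 and 3 and months 3, 6, 9, and 12". Weeks 1 and 3 fall within the initial 3-week titration described under Intervention. They and month 9 are absent from the objective.

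**The concern.** A participant who stops at 1 month is observed for SAEs for a little over a month. One who stops at 6 months is observed for a little over 6 months, and one who continues to 12 months for a little over 12. Observation time is thus fixed by something that happens after randomisation and that treatment may affect. The trial itself treats it as an outcome: the choice to continue beyond 6 months is the acceptability measure, continuation is analysed by logistic regression, and withdrawals are tabulated by arm.

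With the same underlying hazard, the arm that stays on treatment longer will show more participants with an SAE, and the arm with more early stopping will look safer. A reader given only counts could not tell which had happened.

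The ASEC point is of a different kind. A participant who stops for side effects during titration may be off the drug at month 3, the first time point in the tolerability objective. If the outcome is built from that list alone, the assessments closest to early intolerance do not enter it.

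**Working it through.** The article gives no figure for the safety comparison, so there is none to reproduce. The only planned number used is the sample size: 414 / 0.80 = 517.5, rounded up to 518, or 259 per arm.

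**Inputs.** From the article: 6 months of treatment, an optional further 6, and a 7-day tail (about 0.23 month). Assumed: early stopping at 1 month, the stopping and continuation rates, and a constant SAE hazard equal in both arms.

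**Mean observation time.** With *s* the proportion stopping at 1 month and *c* the proportion of the rest who continue to 12 months:

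window = *s* × 1.23 + (1 − *s*) × [(1 − *c*) × 6.23 + *c* × 12.23] months.

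Under equal hazard and low risk, the ratio of windows is close to the expected ratio of participants with an SAE.

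Example, scenario C, first arm: 0.15 × 1.23 + 0.85 × (0.35 × 6.23 + 0.65 × 12.23) = 0.18 + 8.61 = 8.80. Second arm: 0.30 × 1.23 + 0.70 × (0.50 × 6.23 + 0.50 × 12.23) = 0.37 + 6.46 = 6.83. The ratio is 1.29.

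| Scenario (first arm v second arm) | All offered continuation | Half offered (*c* halved) | None offered (*c* = 0) |
|---|---|---|---|
| A: 20% stop early in both; 60% v 45% continue | 8.11 v 7.39, ratio 1.10 | 6.67 v 6.31, ratio 1.06 | 5.23 v 5.23, ratio 1.00 |
| B: 30% v 15% stop early; 50% continue in both | 6.83 v 8.03, ratio 0.85 | 5.78 v 6.76, ratio 0.86 | 4.73 v 5.48, ratio 0.86 |
| C: 15% v 30% stop early; 65% v 50% continue | 8.80 v 6.83, ratio 1.29 | 7.14 v 5.78, ratio 1.23 | 5.48 v 4.73, ratio 1.16 |

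**Early stopping alone, first 26 weeks.** Stoppers are followed to one week after stopping, at week 3 to week 13. With 20% v 10% stopping, the ratio of participants with an SAE is 0.91 to 0.95. With 30% v 15% it is 0.86 to 0.93, and with 40% v 20% it is 0.80 to 0.90. With equal stopping at the same time it is 1.00. Cutting the comparison at 6 months therefore removes the effect of continuation but not that of early stopping, which is why person-time is needed as well.

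**Absolute size.** Take 259 per arm and an assumed 6-month SAE risk of 4%, that is, a hazard of −ln(0.96)/6 = 0.0068 per month. The expected number of participants with an SAE is 259 times the average of 1 − exp(−hazard × window) over the three groups (early stoppers, 6-month completers, continuers).

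- Scenario C, all offered: 15.0 v 11.7, a difference of 3.3. At 2% risk it is 7.5 v 5.9, a difference of 1.7.
- 26 weeks, 40% v 20% stopping at week 3, 4% risk: 6.9 v 8.6, a difference of 1.7. Observing everyone for 26 weeks would give 259 × 0.04 = 10.4 in each arm.

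**ASEC.** The objective lists months 3, 6 and 12. The Safety section lists weeks 1 and 3 and months 3, 6, 9 and 12. The Safety analyses section presents ASEC events by arm and restricts no time points. The lists differ, but nothing removes the early assessments from the safety tables.

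**The case against.** **The window is conventional.** Collecting SAEs on treatment plus a few days is a recognised choice, and the article describes the drug's safety profile as well established. This stands. A reader might infer that the cut-off is an error and that collection should run past stopping. The article does not support that: it would change trial conduct, and amendments go through ethical and regulatory approval. The point concerns how counts from this window are summarised.

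**The detail may be elsewhere.** The article promises a separate analysis plan and sends data-collection detail to an additional file. Person-time tables may be there, and the one-line SAE summary does not rule them out. This stands in part. The window, its two-part wording and the ASEC time points are, however, stated in the article itself.

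**Safety reporting is descriptive.** No SAE test is planned, details of every SAE will be given, and withdrawals appear by arm. This lowers the stakes, but withdrawal counts without dates do not let a reader convert SAE counts into rates.

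**The range is assumption-driven.** This stands. The 1.29 needs continuation offered to everyone, which the article contradicts, and both early stopping and continuation favouring the same arm.

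**The ASEC is not tied to treatment.** A reader might infer that the whole safety comparison depends on who stays on treatment, or that early side-effect data are lost. Neither is supported. The ASEC has no on-treatment cut-off, the hub team telephones non-responders for outstanding data, and the safety summary does not exclude weeks 1 and 3.

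**Conclusion.** The concern holds for two things only: the SAE counts by arm, and the tolerability outcome as defined in the secondary objectives.

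For SAEs, unequal stopping or continuation can shift the raw counts in either direction with no true difference in hazard. The scenarios give ratios of roughly 0.85 to 1.29 if all are offered continuation and 0.86 to 1.23 if half are. Early stopping alone, at the more extreme 40% v 20%, gives 0.80 over 26 weeks. All of this rests on a constant, equal hazard and on assumed rates. If stopping and continuation turn out alike in both arms, there is no distortion. In absolute terms the difference is small, at most about two participants over 6 months and about three with continuation at an assumed 2% to 4% risk. With counts this low, a shift of that size can still colour how the table is read.

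For the ASEC, the finding is a mismatch between the outcome definition and the collection schedule. It is a minor point, but it touches the assessments made during titration.

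**What to change.** 1. Reconcile the two halves of the SAE collection sentence so that it describes one window. No extension of SAE collection after stopping is proposed.
2. Make months 0–6 the main SAE summary by arm. Beside the number of participants with an SAE, give person-time at risk (randomisation to 7 days after the last dose, cut at 6 months) and the rate with a 95% CI.
3. Show months 6–12 separately for those who continued, labelled as a group selected after randomisation.
4. Include the week 1 and week 3 ASEC assessments in the tolerability outcome, for example as each participant's worst severity after randomisation up to month 6, so that the secondary objectives and the Safety section agree.

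The cost is a few extra tables and some wording. The ASEC assessments are already collected, and person-time needs only the stopping dates that the SAE window already relies on. One limit remains: a rate per person-month corrects fully only if the hazard is roughly constant, so the counts should stay beside it.
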